**Fig 1 pone.0343295.g001:**
[figure not shown]
Description of the *med@psy* system user circuit.

Three main categories of psychiatric clinical conditions can lead to consultations at the emergency department: “pure” psychiatric emergencies (acute decompensation of a characterized psychiatric condition), “mixed” emergencies (involving both psychiatric and nonpsychiatric symptoms) and “transient acute states” (intense emotional reactions) [11]. The *med@psy* system mainly addresses acute transient states in which there is no immediate risk of action, such as suicide attempts. It can also address prodromal states or symptomatic exacerbations in patients with an established psychiatric disorder who are being followed by a general practitioner.

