## Materials and methods

### Study design

This study is designed as a prospective, multicenter, nonrandomized comparative cohort study involving two distinct groups: Group 1 and Group 2. Group 1 consisted of patients who presented to the emergency department of the Toulon-La Seyne-sur-Mer Intercommunal Hospital Center (CTS) regardless of whether they were referred by their GP. Group 2 consisted of patients referred by their GP for a psychiatric consultation through the *med@psy* system. Patients will be selected and included from two investigating centers: the *med@psy* system, which is attached to psychiatric practice, and the CTS Emergency Department.

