**Fig 3 pone.0343295.g003:**
[figure not shown]
Description of the study process. (GAF: Global Assessment of Functioning).

For Group 1, after a clinical assessment by a psychiatrist in the emergency department that does not lead to hospitalization, the patient will be given a psychiatric consultation and discharged. The patients were contacted within one week of their visit to the emergency department to be informed about the research. If the patient does not object to participation, they will be contacted at one month and three months post-visit by a psychologist, who will administer the Global Assessment of Functioning (GAF) scale and collect information regarding any follow-up with a psychologist, psychiatrist or general practitioner.

For Group 2, patients will be seen within 48 hours of consulting their GP by a psychiatrist taking part in the *med@psy* system. As part of the research, patients will be contacted within a week of this consultation to be informed about the research. If the patient does not object to participation, they will be contacted at one month and three months after their consultation via the application by the study psychologist, who will administer the GAF scale and collect information regarding any follow-up with a psychologist, psychiatrist or general practitioner.

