The second secondary objective was to compare the overall psychological, social and professional functioning of patients in the two groups via the Global Assessment of Functioning (GAF) scale. The assessment will be conducted by a psychologist during teleconsultations carried out at one and three months. The GAF scale, a component of the Diagnostic and Statistical Manual of Mental Disorders (DSM-IV), provides a global score to subjectively rate the social, occupational, and psychological functioning of an individual. Scores range from 100 (extremely high functioning) to 1 (severely impaired). It incorporates the evaluation of psychological, social, and occupational impairments and considers any physical or social problems that may influence treatment or the severity of the psychiatric condition.

The third secondary objective is to evaluate the adherence of identified medical partners to the use of the *medication* system on the basis of data collected directly from the platform. Adherence will be assessed 12 months after the start of the study: the number of GPs and psychiatrists registered on the *med@psy* system, the number of patients managed *via* the system, the frequency of platform use and the average time between the GP’s referral and the psychiatric consultation provided through the *med@psy* system.

The fourth secondary objective is to characterize the population of patients who received an appointment for a psychiatric consultation within 48 hours *via* the *med@psy* system but who did not attend the scheduled consultation. Patients will be characterized according to the following criteria: age, sex, place of residence, psychiatric diagnosis and reason for referral by the GP.

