### Statistics

All collected data will be summarized via descriptive statistics. Categorical variables will be described as frequencies and percentages, whereas continuous variables will be summarized using the median, minimum, maximum and mean (with standard deviation). Comparisons between groups will be conducted via chi² or Wilcoxon‒Mann‒Whitney tests, depending on the nature of the variable, to ensure comparability between groups. Statistical analyses can then be adjusted, and subgroup analyses can be carried out.

The main objective of this study was to compare the proportion of patients in each group who received outpatient follow-up at one month. A Farrington-Manning test will therefore be used to compare these proportions. The first secondary objective will involve a similar comparison of outpatient follow-up at three months between the two groups.

At one and three months, telephone interviews will be conducted by a psychologist to assess the Global Functioning Scale (GAF) score. The distribution of the GAF score between groups will be compared via a nonparametric Wilcoxon Mann‒Whitney test.

At 3 and 12 months, questionnaires will be administered to users of the *med@psy* system (GP and psychiatrists) to assess their overall satisfaction and report any concerns they may have.

System adherence will be assessed 12 months after the start of the study, on the basis of the number of GPs and psychiatrists registered on the platform, the number of patients treated *via* the system, the frequency of use, and the time elapsed between referral and the psychiatric consultation offered *via* the *med@psy* system.

Additionally, the characteristics (age, sex, pathology and reason for referral) of patients who obtained an appointment for a psychiatric consultation within 48 hours via the *med@psy* system but did not attend will be described. These nonincluded patients will have been informed of the research in advance and must not have expressed any opposition to their data being processed. The statistical significance threshold is 5%.

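### GAF is compared between nonrandomised cohorts by an unadjusted Wilcoxon test with no index score described, so a difference in functioning at entry cannot be separated from a pathway effect

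*Protocol article*

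**What the plan says.** The Study design section describes a "prospective, multicenter, nonrandomized comparative cohort study involving two distinct groups". Group 1 presents to the psychiatric emergency department, with or without a GP referral. Group 2 is referred by GPs into med@psy, which, according to the Introduction (text under Fig 1), "mainly addresses acute transient states in which there is no immediate risk of action"; the example given there is suicide attempts.

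The second secondary objective (Outcomes) is to compare functioning between the two groups on the GAF. On timing, the same section says "The assessment will be conducted by a psychologist during teleconsultations carried out at one and three months". The Procedure section (text under Fig 3) agrees for Group 1: "they will be contacted at one month and three months post-visit by a psychologist, who will administer the Global Assessment of Functioning (GAF) scale". It sets the same two contacts for Group 2. No GAF rating at the index consultation appears in the text. The schedule figure is not available to check.

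On analysis, the Statistics section states: "The distribution of the GAF score between groups will be compared via a nonparametric Wilcoxon" Mann-Whitney test. Earlier in that section, chi² or Wilcoxon tests are planned between groups, "depending on the nature of the variable, to ensure comparability between groups", followed by the sentence "Statistical analyses can then be adjusted, and subgroup analyses can be carried out".

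**The concern.** The named test takes no covariates, and the outcome has no described starting value. Patients who go to an emergency department and patients whom GPs select for a scheduled consultation may well function differently on the day they enter. If they do, part of that gap will still be present at one and three months, and the Wilcoxon test will register it whatever the pathway did.

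The sentence permitting adjustment does not settle this. It states a possibility, not a plan, and does not say that it covers GAF. It also follows significance tests of comparability. A non-significant test does not show that groups are alike, and no such test can examine entry functioning if entry functioning was not recorded.

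At stake is the reading of a secondary objective. A significant GAF difference could be taken as a benefit or harm of a pathway when it reflects who entered it. The rank test as described also yields no adjusted difference with an interval.

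**Working it through.** **Plan's own figure.** The article gives no expected difference, SD or power for GAF. Its only sample-size figure, 217 per group, is for the primary outcome (10% v 20%, power 90%). The pooled normal formula with one-sided alpha of 5% reproduces it:

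n = [1.645·√(2·0.15·0.85) + 1.282·√(0.09 + 0.16)]² / 0.10² = (0.831 + 0.641)² / 0.01 ≈ 217.

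Here 217 serves only as the number of patients per group with a GAF score.

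**Inputs for the illustration**
- From the article: 217 per group; 5% significance threshold.
- Assumed, not in the documents: two-sided test; GAF SD 12 at entry and at follow-up; entry-to-follow-up correlation r of 0.3, 0.5 or 0.7; entry gaps of 0 to 8 points; no pathway effect.

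**Simulation.** There were 2,000 replicates per setting, with scores rounded and limited to 1 to 100. Follow-up GAF depends on entry GAF through r and on nothing else. The table shows the share of studies in which the unadjusted Wilcoxon test is significant.

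| Entry gap (points) | r = 0.3 | r = 0.5 | r = 0.7 |
|---|---|---|---|
| 0 | 5.8% | 5.4% | 5.0% |
| 2 | 7.8% | 12.6% | 21.8% |
| 3 | 11.2% | 22.1% | 42.2% |
| 5 | 26.8% | 55.7% | 85.1% |
| 8 | 53.5% | 92.6% | 99.6% |

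The spurious mean difference is about r × gap. For a 5-point gap it was 1.52, 2.48 and 3.50 points; for a 2-point gap, 0.63, 0.99 and 1.38. When the same data were analysed by a linear model with entry GAF as a covariate, the rejection rate was 4.4% to 5.6% in every setting. This shows what an index score would contribute. It does not show what adjustment for age, sex or diagnosis would achieve.

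**Full persistence, by formula.** z = (gap/SD) / √(2/217) × √0.955, where √(2/217) = 0.0960, 0.955 is the Wilcoxon efficiency for normal data, and power = Φ(z − 1.96).
- 5 points, SD 15: z = 3.39, power 92%.
- 5 points, SD 12: z = 4.24, power 99%.
- 5 points, SD 10: z = 5.09, power above 99%.
- 2 points, SD 15: z = 1.36, power 27%.
- 2 points, SD 10: z = 2.04, power 53%.

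At SD 12, 90% power needs z = 1.96 + 1.28 = 3.24, so a persisting share of 3.24/4.24 = 0.76 of a 5-point gap. That is above the 0.3 to 0.7 range assumed in the table.

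**The case against.** The strongest reply is that the article does allow adjusted analyses after a comparability check, and that covariates and models are normally left to an analysis plan, which is not shown. That stands against reading the article as ruling adjustment out. It does not remove the point. What the article states positively for GAF is an unadjusted test, and no later analysis plan can adjust for an index score that was never recorded.

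Second, eligibility narrows the gap. Both groups exclude patients referred for a suicide attempt, those under current psychiatrist follow-up, those under care orders and those with no declared GP. Group 1 must also have been discharged home, and med@psy may take symptomatic exacerbations of established disorders. This stands: an entry difference is plausible, but the documents support no size or direction for it.

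Third, the objective is worded as a comparison of the groups, and the Discussion says the clinical effectiveness of the outpatient care was not evaluated. This also stands. A reader might infer that the objective cannot be answered at all, but a descriptive comparison can be. What is missing is a statement that it is only descriptive. The limitations mention diagnostic heterogeneity, but not confounding by entry severity.

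Fourth, collecting an index GAF for research conflicts with the recruitment procedure. Patients are identified after the consultation, and non-opposition must precede any research procedure. Inclusion was also due to end by 3 March 2026. This stands, and no such rating is proposed here.

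**Conclusion.** The point holds in a limited form. With nonrandomised cohorts, no index GAF described and adjustment left optional and unspecified, the stated Wilcoxon comparison cannot separate a difference at entry from a pathway effect.

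Two stronger readings are not supported:
- A reader might infer that any severity difference will be reported as a pathway effect. The permissive adjustment sentence and the absence of a stated causal claim for GAF speak against that.
- A reader might infer that even a modest gap will almost surely be significant. A 2-point gap gives 8% to 22% under partial persistence at SD 12, and only 27% to 53% under full persistence at SD 15 to 10. Figures of 92% and above for a 5-point gap come from assuming that it persists in full.

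The range to carry forward for a 5-point gap is 27% to 85%. The gap, SD and correlation are assumptions, so this is an illustration and not a forecast. The estimate is biased by about r × gap even when the test is not significant. The point concerns a secondary objective and does not touch the primary analysis.

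**What to change.** - Make the main GAF analysis a covariate-adjusted or propensity-weighted model of the one- and three-month scores, and report adjusted mean differences with 95% CI at each time.
- Fix the covariates before analysis. Choose them from entry characteristics available in the sources listed under Data, for example age, sex, diagnosis and reason for consultation or referral, after confirming that each is recorded comparably in both cohorts.
- Keep the Wilcoxon-Mann-Whitney test as a crude supporting result.
- State that, without an index GAF, residual confounding by entry severity remains, and that the comparison is descriptive and supports no claim of a pathway effect on functioning.
- Use an index GAF as a covariate only if it is already in the routine records. Do not add a research rating at the index consultation.

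The cost is slightly more analysis work and a more modest secondary conclusion. No new patient contact is needed. Follow-up is scheduled to finish by 10 June 2026 and results are expected in September 2026, so the wording should be settled before the GAF data are analysed.

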### Data

To collect the data required for the study, several databases will be consulted: the *med@med* digital platform, medical records of patients attending the CTS psychiatric emergency department, and data collected directly from patients during teleconsultations.

### Ethical considations

This protocol has been submitted to and accepted by the Ethics Committee (CPP Ile de France III – 2024-A01115-42). All research procedures were conducted in accordance with the principles outlined in the Declaration of Helsinki. The study has been registered on ClinicalTrials.gov under the identifier NCT06581874. Prior to participation, all patients received both oral and written information about the study and were included only if they did not express any objection to participation.

This study was conducted as a Category 3 research involving human participants (RIPH 3) under French law (Loi Jardé). For this type of study, informed consent is not required. Participants were provided with clear and appropriate information about the study objectives, the data collected, and their right to object to participation. Inclusion was based on the absence of objection. Investigator’s team assessed participants’ capacity to understand the information and express opposition at the time of inclusion; individuals unable to do so were not included. This information and non-opposition procedure was approved by the Ethics Committee [CPP Ile de France III] (approval number: 24.02552.000635).

### Status

Patient enrollment began on 22 January 2025. The first patient was included on March 3, 2025.

Inclusion will continue for 12 months, with final enrollment expected by 3 March 2026. Data collection and follow-up are scheduled to be completed by 10 June 2026. The results are expected in September 2026.

## Discussion

This study aimed to evaluate the implementation of outpatient follow-up after consultation with a psychiatrist via the *med@psy* system compared with follow-up after a psychiatric evaluation in the emergency department of the CTS. The *med@psy* system is a collaborative care system that enables GPs to schedule a psychiatrist consultation for their patients within 48 hours.

This study evaluated a new care pathway initiated by GPs, positioned as a potential alternative to emergency psychiatric consultation. It will be carried out under real-world conditions, taking into account existing difficulties and barriers to implementation. One potential risk identified is the possibility that GPs may not adopt or consistently use the *med@psy* system, which could affect the recruitment process and limit data collection.

The *med@psy* system was developed to address difficulties in accessing secondary mental health care, particularly for patients initially managed in primary care. Numerous barriers to the integration of mental health services into the primary care setting have been identified. This includes a low level of interest in mental health care provision among some GPs, increased workload and limited time, insufficient local mental health support, and limited resources for service delivery [12]. However, there are also enablers, such as the ability to understand the patient holistically and the convenience of service provision [12]. This new integrated care pathway via the *med@psy* system responds to facilitators while limiting obstacles. Referral to the platform is simple and takes less than 5 minutes. The *med@psy* system operates on a participatory and voluntary basis. This study highlights the crucial role of psychiatrists in primary care and provides information about the local mental health network. It is advisable to create and maintain up-to-date databases that provide GPs with information about psychiatrist availability, areas of expertise, and modes of practice, as this helps align referrals with appropriate psychiatric services [13]. Timely access to psychiatric consultations helps reduce frustration for both GPs and patients [13]. The *med@psy* system provides information about the various available referrals. Local educational interventions involving secondary care specialists and structured referral forms have also been shown to impact referral rates [14]. In addition, the *med@psy* system integrates reimbursement systems for unscheduled care, thereby enabling its use by GPs and psychiatrists. This approach helps to overcome financial barriers that might impede its implementation [15]. Taken together, these elements represent strong arguments in favor of the adoption and sustained use of the *med@psy* system by GPs.

This new care pathway benefits from being based on the existing network of healthcare practitioners while considering the realities of primary care practice. We also assume that this *med@psy* system goes beyond traditional interprofessional collaboration and constitutes a model of “integrated” care. The World Health Organization (WHO) defines integrated care as follows: *“The management and delivery of health services so that people benefit from a continuum of health promotion, disease prevention, diagnosis, treatment, disease management, rehabilitation and palliative care, across the different levels and sites of care in the health system, and according to their needs throughout life”* [16]. Other definitions have also been set out [17]. An essential aspect of integrated care is coordinating care effectively according to people’s needs [17]. It is therefore not just a question of collaboration but also of integrating new practices into primary care that considers the patient’s interests. Referring the patient directly to the psychiatric emergency department is a typical default pathway for the population and is sometimes not patient-centered.

This study has several limitations. It is subject to the capacity of the two pathways to take on the active files of patients. Factors such as regional medical demographics (general practitioners and psychiatrists) and the organizational structure of the CTS emergency department are beyond our control. In terms of patient profiles, the study did not focus on a single diagnostic category, thereby introducing clinical heterogeneity. The effectiveness of the *med@psy system* also relies on its appropriate use by GPs; excessive or indiscriminate referrals could risk overwhelming the system. Furthermore, the broader healthcare context including potential reforms or changes to reimbursement models may significantly influence care pathways but falls outside the scope of our control. Importantly, this study assesses only two specific types of care pathways, each with particular prerequisites. For example, the collaborative model requires patients to have an identified GP that excludes patients without a registered GP or those already engaged in psychiatrist outpatient care. Finally, the study did not evaluate patient adherence to follow-up or the clinical effectiveness of the outpatient care provided.

## Abbreviations

CTS: Toulon - La Seyne-sur-Mer Intercommunal Hospital Center
GPs: General practitioners
GAF: Global Assessment of Functioning
WHO: World Health Organization.
